### Interim analyses {21b}

Two “formal interim analysis” meetings will be held by Data and Safety Monitoring Board (DSMB) by teleconference (or face-to-face, if possible) to review data relating to treatment efficacy, patient safety, and quality of trial conduct.

A recommendation to discontinue INTERACT3 prematurely will be based upon there being clear evidence that the treatment provides protection or causes harm for an important clinical outcome.

The DSMB will work on the principle that a difference of at least 3 standard errors in an interim analysis of a major outcome event (e.g., death from all causes or independent survival at 6 months) between patients allocated to the intensive or the control group, to justify halting, or modifying the study, before the planned completion of recruitment. Given the minimal impact of this approach on the type-I error rate, no adjustment is made to the final significance level [29].

### Methods for additional analyses {20b}

#### Substudy—effects of treatment of hematoma growth in ICH

The effects of treatment on hematoma expansion and other indices including perihematomal edema will be evaluated in a subsample of 1000 patients (the earliest 7 recruitments in each of the control and intensive groups, respectively, for each site). Apart from the baseline CT scan, repeat CT scans (24 ± 3 h and 7 days) are required. CT imaging will be conducted according to standardized techniques and uploaded to purpose-built server, either directly from the hospital site (if they have suitable broadband internet) or via the RCC office. The LCC will keep a hard copy in an uncompressed DICOM format onto a CD-ROM for monitor site verification. The imaging data will be analyzed centrally by experts who will be kept blind to the treatment allocation. The primary efficacy measure is proportional absolute and relative changes (“growth”) in hematoma and perihematomal volumes according to standard measures at 24 h. Background measures of cerebral small vessel disease and “brain frailty” will also be recorded. Clinical outcomes are assessed over 6 months.

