## Trial design {8}

The INTERACT3 study is an international, multicenter, prospective, stepped-wedge, cluster-randomized controlled, blinded outcome assessed (PROBE) trial, which is being conducted through a network of investigators in LMICs. After participating hospital sites commence in a usual care “control” phase, they progressively transfer to the intervention (care bundle) at pre-determined stages through random allocation into 3 groups (Fig. 1). In each phase, hospitals aim to reach an average target of 19 consecutive ICH patients who fulfill the eligibility criteria, but this number may vary from 1 to 50 patients according to service configuration and patient volumes. However, each phase has a 3-month time limit, to ensure that the intervention period of the study is completed over 12 months. The study design is summarized in Fig. 2.

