### Additional consent provisions for collection and use of participant data and biological specimens {26b}

The study consent process includes permission for additional analysis of the collected data for systematic reviews and individual patient data pooling projects. In a subset of 1000 consecutive patients across sites, all brain imaging over a 7–10-day period are collected and uploaded in Digital Imaging and Communications in Medicine (DICOM) format for analysis of the characteristics of the ICH and underlying brain structure at a core imaging laboratory at The George Institute for Global Health (TGI), Sydney, Australia. No biological specimens are collected.

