### Sample size {14}

The study is designed with 90% power (*α* = 0.05) to detect a 20% reduction in the odds (common odds ratio of 0.80) of worse functional outcome using ordinal logistic regression. Assuming a distribution of mRS in the usual care control arm that is similar to that observed in the standard BP control arm of the INTERACT2 study [7] (i.e., 7.6%, 18.0%, 18.8%, 16.6%, 19.0%, 8.0%, and 12.0% for mRS scores of 0 to 6, respectively), this corresponds to a 5.6% absolute improvement in the proportion of patients experiencing a poor outcome (mRS scores 3-6), that is from 55.6% down to 50%. This also translates into a 10% relative risk reduction (relative risk of 0.90). The combination of interventions as part of an intensive care bundle is assumed to provide a greater treatment effect than the use of BP lowering alone (in INTERACT2, the treatment effect was 4% absolute).

The study plans to recruit 110 sites in a stepped-wedge design consisting of 3 groups and 4 phases. Each group would, therefore, include approximately 36 sites. Assuming an intraclass correlation coefficient (ICC) of 0.044, which is similar to that of the INTERACT2 [7] and Head Position in Acute Stroke Trial (HeadPoST) [25] studies that included large numbers of hospitals in China, each site would be required to recruit an average of 18 patients per phase. Accounting for 5% of participants with a missing outcome, each site would need to target an average of 19 patients per phase, thus leading to a total sample size of 8360 patients (110 sites × 4 phases × 19 patients).

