We recognize there will be variability in the number of patients who will be recruited at each site, with very large hospitals recruiting as many as 50 patients per phase while smaller hospitals may only recruit a few patients per phase. If the sample size was inflated to accommodate this issue as has been used in parallel cluster trials [26] (e.g., using an inflation factor of approximately 1.3), the sample size would need to reflect 25 patients per site per phase (i.e., 11,000 patients in total). However, given that this adjustment would be a very conservative scenario and that the effect of variability in cluster sizes is expected to be mostly mitigated by the randomization process, including stratification by size [27], we have elected to maintain the target average of 19 patients per site per phase for a total sample size of 8360 patients. Assuming a worst-case scenario for the effect of cluster size variability on power, this sample size would still provide at least 80% power to determine the proposed treatment effect.

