### Implementation {16c}

In phase 1, all hospitals will be observed under usual care “control” conditions according to usual management of ICH patients. In phase 2, the first cluster of hospitals (group 1) will start implementing the intervention (care bundle), and then sequentially, groups 2 and 3 will start implementing the interventional package in phases 3 and 4, respectively, so that by phase 4, all hospitals will be receiving the intervention, with those in group 1 having the intervention for longest and those in group 3, the shortest. Once the site has completed the necessary control usual care observational period, they will receive training on the application of the care bundle intervention during the study. The site investigator will be informed to pause enrolment when the patient number or study duration in control phase has reached the pre-specified target, and then will be instructed to transfer over to the intervention phase after a recruitment interval of 7–10 days.

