## Statistics methods

### Statistical methods for primary and secondary outcomes {20a}

All analyses will be undertaken at the patient level on an intention-to-treat (ITT) basis at each site using generalized estimating equations (GEE) or random-effects regression to account for clustering. The primary outcome of a shift (improvement) in scores on the mRS at 6 months will be analyzed by means of an ordinal logistic regression, with mRS as a dependent variable with 7 levels (0 [no residual symptom] to 6 [death]). The model will include the trial phase (1 to 4), the randomized arm (control or intervention) corresponding to each phase, and the size of the site (as used in the stratification). The secondary outcome of neurological change at 7 days will be analyzed with the same method [28]. Binary and continuous secondary outcomes will be analyzed using a similar approach but using logistic and linear regression, respectively.

All analyses will be adjusted for clustering within center, hospital size (stratification variable), and for trial phase. In addition, sensitivity analyses will be conducted after considering potential prognostic variables as well as the effect of time to adjust for potential background secular trends, including the potential impact of the COVID-19 pandemic.

No adjustment for multiplicity is planned as there are only a small number of pre-specified efficacy outcomes being investigated. A detailed statistical analysis plan will be finalized before unblinding and database locked and posted on a pre-print server.

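### The hematoma-growth substudy draws nearly all its controls from phase 1, so its phase-adjusted effect is unidentifiable or weak, and its selection rule yields up to 1540 patients, not 1000

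*Protocol article*

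**What the plan says.** The substudy section under {20b} fixes the imaging sample as "a subsample of 1000 patients (the earliest 7 recruitments in each of the control and intensive groups, respectively, for each site". Section {26b} gives the same total but selects it differently: "In a subset of 1000 consecutive patients across sites".

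The design around it is as follows.

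- Implementation {16c}: "In phase 1, all hospitals will be observed under usual care" conditions. Groups 1, 2 and 3 then cross over in phases 2, 3 and 4.
- Sample size {14}: "The study plans to recruit 110 sites in a stepped-wedge design consisting of 3 groups and 4 phases", with the total built from an average of 19 per site-phase: "thus leading to a total sample size of 8360 patients (110 sites × 4 phases × 19 patients".
- Trial design {8}, on the number per phase: "this number may vary from 1 to 50 patients according to service configuration and patient volumes". Sample size {14} adds that "smaller hospitals may only recruit a few patients per phase".
- Statistical methods {20a}: "All analyses will be adjusted for clustering within center, hospital size (stratification variable), and for trial phase". The model carries phase (1 to 4) and arm. The article does not say whether phase is categorical or linear, and gives no separate model for the substudy.

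Whether the bundle reduces hematoma growth and perihematomal edema is one of the listed research questions.

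**The concern.** In this one-direction stepped wedge, the randomised information comes mainly from phases 2 and 3. There, some groups have crossed over while others are still controls. Quotas set by site and arm, and filled with the earliest patients, pass over those phases on the control side. A site at planned volume fills its seven control places in phase 1 and contributes no control scan afterwards, even if it remains a control for one or two further phases.

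The imaging comparison then becomes largely phase 1 against later phases within sites, which is a before-after contrast. Section {20a} itself anticipates secular trends, including COVID-19, and such trends would be mixed with the bundle effect. Adjusting for phase removes most or all of the information on arm. Leaving phase out gives up the protection of the stepped wedge.

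Separately, the stated size does not follow from the stated rule, and the two sections describe different samples.

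**Working it through.** **Inputs.** From {14}: 110 sites, 3 groups, 4 phases, average 19 per site-phase, ICC 0.044. The ICC is planned for the mRS; its use for hematoma growth is my assumption. From {16c}: the crossover times. From {20b}: 7 control and 7 intervention patients per site. From {8} and {14}: site-phase counts of 1 to 50, with some sites recruiting few. The article gives no CV of site size; I take 0.4 to 1.0.

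**1. Count.** The main total reproduces: 110 × 4 × 19 = 8360. The substudy total does not.

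- 110 × (7 + 7) = 1540, which is 54% above 1000.
- With the 93 sites that had enrolled by 31 December 2020: 93 × 14 = 1302.
- 1000 / 14 = 71.4, and 71 × 14 = 994. The article does not limit the substudy to about 71 sites.
- 1540 is a ceiling. With variable site sizes some quotas stay unfilled and the total is about 1360 to 1530.

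**2. Phase layout at planned recruitment** (19 per site-phase; groups of 37, 37 and 36 sites).

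| | Phase 1 | Phase 2 | Phase 3 | Phase 4 |
|---|---|---|---|---|
| Control | 110 × 7 = 770 | 0 | 0 | 0 |
| Intervention | 0 | 37 × 7 = 259 | 37 × 7 = 259 | 36 × 7 = 252 |

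For every selected patient, arm = I(phase 2) + I(phase 3) + I(phase 4). The design matrix (intercept, arm, three phase indicators) has rank 4 of 5. The arm effect adjusted for categorical phase is not identifiable. The layout is the same for any recruitment of at least 7 per site-phase.

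**3. Variable site sizes.** With outcome SD 1 and V_i = (1 − ρ)I + ρJ for site i, ρ = 0.044, the variance of the arm effect is the arm element of (Σ X_i′ V_i⁻¹ X_i)⁻¹. Single simulated draws, site-phase counts limited to 1 to 50:

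| Site sizes (assumed) | Substudy N | Controls in phases 2–3 | SE, this rule | SE, similar N spread over phases |
|---|---|---|---|---|
| Capacity strata, Poisson | 1531 | 7 of 763 (0.9%) | 0.386 | 0.083 |
| Gamma, CV 0.5 | 1513 | 21 of 760 (2.8%) | 0.233 | 0.082 |
| Gamma, CV 0.8 | 1486 | 33 of 753 (4.4%) | 0.190 | 0.082 |
| Gamma, CV 1.0 | 1417 | 65 of 713 (9.1%) | 0.146 | 0.086 |

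Over repeated runs at CV 0.4 to 1.0, about 1 to 7% of controls typically come from phases 2 and 3 (the last draw above is at the high end). The SE is about 0.15 to 0.46 SD in most runs. At CV 0.4 a few runs are still singular. The late controls all come from low-volume hospitals.

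**4. Alternative.** Two per site-phase gives 110 × 4 × 2 = 880 scans (SE about 0.10 SD); three gives 1320 (SE about 0.09 SD). Later-phase controls would then be (37 + 36) × 2 = 146 to 73 × 3 = 219 in phase 2, and 36 × 2 = 72 to 36 × 3 = 108 in phase 3.

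**5. Other time adjustments under the present rule.** A linear phase term is estimable even in the layout of step 2: SE = √0.0117 = 0.108 SD. With calendar-quarter effects and site starts spread at random over an assumed 2, 4 or 8 quarters, about 51%, 74% or 85% of controls fall in a quarter that also has intervention scans, and the SE is 0.11, 0.07 or 0.06 SD. Only simultaneous starts are singular.

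**The case against.** A reader might infer that the substudy has no concurrent controls and that its effect cannot be estimated at all. The documents do not support that, for three reasons.

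- Phase is counted within sites and is not calendar time. Enrolment runs from December 2017 to March 2022, each phase is limited to 3 months, and sites outside China were to roll out in early 2021. Phase 1 controls at later sites overlap in calendar time with treated patients at earlier sites. Section {20a} also plans sensitivity analyses for time.
- The rank failure needs categorical phase and at least 7 phase 1 patients at every site. The coding is not stated, and {8} and {14} allow smaller sites.
- The phase adjustment stands under the primary and secondary outcomes in {20a}, whereas the substudy stands under {20b}. The SAP, which is not shown, may specify another model.

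All three points stand and limit the claim. They do not remove it. A linear phase term assumes that the secular trend is linear. Calendar adjustment compares earlier-starting with later-starting sites, and the start date was not the randomised element. The small sites leave only a handful of late controls. The selection rule is fixed in the protocol, and no SAP can supply phase 2 and 3 controls that were never selected.

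It is also fair to say that extra scans do not bias anything, so the count alone would be a wording matter.

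**Conclusion.** The concern holds in a limited form and should be fixed. At planned recruitment the rule places all controls in phase 1, and the effect adjusted for categorical phase is not identifiable. With realistic small sites it is usually estimable but weak: SE about 0.15 to 0.46 SD in most runs, against about 0.09 to 0.10 SD for 880 to 1320 scans spread over phases. These figures assume ICC 0.044 for this outcome, site-size CV 0.4 to 1.0, and that the phase adjustment in {20a} extends to the substudy. Linear or calendar-time adjustment can recover information, but without relying on the randomised step.

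The stated 1000 does not follow from the rule, which gives up to 1540, or about 1360 to 1530 with variable sites. Sections {20b} and {26b} agree on 1000 and differ in how the patients are chosen.

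A reader might also infer that the trial's main result is at risk. It is not: the primary mRS analysis, the clinical secondary outcomes and safety do not use this sample.

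**What to change.** - For sites and phases still to recruit, select the first 2 or 3 consecutive patients in each site-phase. Groups 2 and 3 then contribute control scans in phases 2 and 3. That is 8 to 12 scanned patients per site instead of 14, or 880 to 1320 over 110 sites.
- State one selection rule, and an N that matches it, in both {20b} and {26b}.
- Do not fill the gap with later-phase controls chosen because repeat CTs happen to exist. Being rescanned depends on survival and possibly on deterioration, so this could add outcome-related selection.
- For sites already sampled under the present rule, describe the contrast as mainly before-after and adjust it for calendar time.

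The cost is a revised sampling list part-way through the trial. The correction can only be partial, because 5917 participants at 93 sites had already been enrolled by 31 December 2020.

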#### Process evaluation

In order to explore how the care bundle, a complex intervention, is implemented, as well as to understand clinicians’ perspectives, a prospective process evaluation will be conducted alongside the roll-out of the trial. Intervention fidelity, reach, dose, adoption, feasibility, and appropriateness of the goal-directed care bundle will be evaluated within the trial. Contextual conditions (current policies, settings resources, etc.) that may have impacted on the quality of the implementation are being assessed.

A mixed methods analytical approach is being used to address the objectives of process evaluation, with questions and indicators informed by the process evaluation framework of the Medical Research Council (MRC) [30]. The normalization process theory (NPT), which has been used for assessing how guidelines are embedded into routine practice, will serve as a conceptual framework to explore systematically how overall and for each of the interventions were adopted into patient care [31]. To assess the implementation and mechanism of impact of the interventions, semi-structured interviews and non-participants observations will be conducted among the primary implementers (physicians and nurses) using structured interview guides and observation templates. Focus group discussions will be conducted with project operation staff and site principal investigators to explore facilitators and barriers to the care bundle delivery by different stakeholders. Observational records, including hospital organization questionnaires, routine monitoring data, field notes, and CRFs, will also be used to triangulate qualitative findings to assess implementation quality, acceptability of the care bundle, and contextual factors, which may have impacted on outcomes. Sites involved in the process evaluations will be determined by purposive sampling in accordance with the pre-specified criteria to achieve representativeness. Results of the process evaluation will be used to monitor and document project implementation, as well as identify barriers, which the coordinating team uses to address in a timely fashion, such as increasing the confidence of clinicians in managing the intervention by providing them with additional training.

### Methods in analysis to handle protocol non-adherence and any statistical methods to handle missing data {20c}

All analyses including the primary analysis, will be conducted on the ITT population and using all available data. If more than 5% of patients have a missing primary outcome, we will use multiple imputations for sensitivity analysis.

### Plans to give access to the full protocol, participant-level data, and statistical code {31c}

The data collected is owned by the TSC. Datasets generated and/or analyzed will be available to all study investigators, and to investigators at other institutions around the world, according to a data sharing agreement. Data sharing will be available from 12 months after publication of the main results. Investigators are to make a formal request for data sharing through the Global Research Committee (GRC) of TGI, and according to a data sharing policy (https://georgeinstitute.sharepoint.com/TGIPolicy/Data%20Sharing%20Policy.pdf). Access will be controlled by the Principal Investigators (PIs) with the approval of the TSC.

## Oversight and monitoring

### Composition of the coordinating center and TSC {5d}

#### TSC

The TSC (independent Chair) will comprise independent members, the principal investigators, national leaders, expert academic researchers, patient representatives, and an observer from Medical Research Council (MRC) and will be governed by a Charter (Appendix 4). The TSC is responsible for overseeing the execution of the study design, protocol, data collection, and analysis plans, as well as publications.

#### CCC

The CCC is based at TGI China, supported by project staff, and is responsible for the day-to-day management of the study, data and project management, committee coordination, assistance with ethics committee and regulatory applications, protocol and procedures for training of participating sites, overseeing of initiation visits and activation of participating centers, monitoring of data quality and adherence to protocol, applicable guidelines and regulations, preparation of study data for analysis, and publication.

### Composition of the data monitoring committee, its role, and reporting structure {21a}

#### DSMB

The DSMB is independent of the sponsor and responsible for reviewing the safety, ethics, and outcomes of the study. The DSMB is governed by a Charter outlining responsibilities, procedures, and confidentiality, and reviews the accumulating unblinded data at regular intervals (Appendix 5).

### SAE reporting and harms {22}

An SAE is defined according to standard convention as any untoward medical occurrence that results in any of the following: (i) results in death; (ii) is life threatening in the opinion of the Investigator (at the time of the event); (iii) requires admission to hospital or prolongation of an existing hospital stay; (iv) results in persistent or significant disability or incapacity; (v) results in congenital anomaly or birth defect; or (vi) is an important medical event in the opinion of the Investigator that is not immediately life-threatening and does not result in death or hospitalization but which may jeopardize the patient or may require intervention to prevent one of the other listed outcomes.

An SAE form is provided for recording details that includes the event diagnosis, classification of the event using standard definitions, the Investigator’s opinion on the causal relationship to the care bundle, and the timing of the event. The Investigator will be responsible for ensuring that details of investigations and outcomes of an SAE are finalized. The SAE should be documented in the medical records or patient file, and signed and dated by the investigator, for audit and monitoring. All SAEs are reviewed by a medical monitor assigned to the trial. Safety outcomes are reported to the presiding Ethics Committees in line with their requirements every 6 months, as well as for review by the DMSB at each meeting.

